## Abstract

**Background:**

Zoonotic infectious disease risk arises at human–animal–environment interfaces where pathogen spillover can occur. Rural communities living in biodiverse settings may experience frequent contact with wildlife and shared environments through livelihoods, food practices, and economic activities. Reducing spillover risk and strengthening pandemic prevention requires both structural and individual-level change. Community-based interventions that promote awareness, risk perception, self-efficacy, pro-environmental behaviour, and safe coexistence with wildlife may support prevention by shifting behavioural determinants of zoonotic disease risk. The Saan Suk intervention was co-developed with rural communities in Thailand using a Human-Centred Design approach and is grounded in the Health Belief Model and One Health principles. The intervention is intended to be feasible, acceptable, and deliverable through Thailand’s established Village Health Volunteer (VHV) system.

**Methods:**

This protocol describes a parallel-arm, cluster-randomised controlled superiority trial that will be conducted during July – October 2026, in Chanthaburi Province, Thailand. 24 villages will be equally randomised to the Saan Suk intervention or the current practice (control). In intervention villages, trained VHVs will deliver, once a week over four weeks, a multimodal One Health educational intervention designed to improve knowledge of zoonotic spillover, promote protective behaviours, reduce risky wildlife-related contacts, and support respectful coexistence with wildlife. Trained outcome assessment teams will conduct structured interviews with 42 adult participants per village, yielding a total sample size of 1,008 participants. The sample size was calculated for the primary outcome, accounting for clustering, with 90% power to detect a medium effect size (6 points on the 0–100 knowledge scale) at a significance level of 0.05, accounting for a design effect with an ICC of 0.028. The primary outcome is knowledge of zoonotic spillover, transmission pathways, risk factors, protective and risky behaviours, and safe coexistence with wildlife. Secondary outcomes include attitudes, self-efficacy, preventive and risky behaviours, and reported contacts with major local reservoir hosts. A structured questionnaire was developed, expert-reviewed, and piloted for the outcome assessment. Outcomes will be analysed using mixed-effects regression models with random effects for village and adjustment for relevant pre-specified confounders. Primary analyses will follow the intention-to-treat principle.

**Discussion:**

This trial will evaluate whether a co-designed, VHV-delivered One Health educational programme can improve knowledge of zoonotic disease prevention and behavioural determinants in rural communities living in close contact with wildlife and shared ecosystems. If effective and feasible, Saan Suk could inform integration into routine VHV training and community-based zoonotic disease and pandemic prevention strategies.

**Trial Registration:**

The Saan Suk trial is registered with the German Clinical Trials Register (DRKS). Registration ID: DRKS00038582; date of registration: 11 May 2026.

## Introduction

Zoonotic infectious diseases, transmissible from vertebrate animals to humans [1], can lead to large-scale outbreaks, as seen with COVID-19 (SARS-CoV-2) [2], the Middle East respiratory syndrome coronavirus (MERS-CoV) [3], and Influenza A (H1N1) [4], which generated severe impacts on public health and economy at a global scale [2]. Recent outbreaks of Andes Hantavirus linked to international cruise travel [5] and the ongoing Ebola Bundibugyo outbreak in the Democratic Republic of Congo and Uganda [6] further underscore the continued public health relevance of zoonotic infectious diseases and zoonotic pathogen spillover. Zoonotic spillover arises from a complex alignment of socio-ecological drivers at local and macro-ecological scales [7]. Human-driven changes, such as deforestation, habitat fragmentation, climate change, intensive farming, wildlife trade, and hunting [8,9], have contributed to increased human-animal interaction and exposure to pathogens, creating favourable conditions for zoonotic spillover [10]. In this context, One Health and EcoHealth approaches emphasise the interconnectedness of humans, animals, and the environment [11,12] and are essential for implementing effective zoonoses prevention, surveillance, and control measures [1]. Thailand has been recognised as a hotspot for biodiversity and human-wildlife interactions and is at risk of zoonotic disease emergence in Asia [13,14]. The country faces endemic zoonotic and vector-borne diseases (e.g., dengue fever, Chikungunya, Japanese encephalitis, simian malaria, and rabies) [15,16], and novel viruses identified in wildlife [17].

Community engagement interventions based on One Health approaches have effectively addressed public health challenges, especially in rural settings [18]. For instance, the “Lawa Project” [19,20] in Thailand combined school and community education, training of Village Health Volunteers (VHVs), ecosystem monitoring, and disease surveillance, significantly reducing opisthorchiasis in villages in northeast Thailand. VHVs were introduced into the Thai health system in the late 1970s to connect the formal health system with the community, becoming an internationally recognised public health model [21]. Managed by the Thai Ministry of Public Health (MOPH) under the Primary Healthcare Division, the programme encourages trusted community members living and working in the village to apply for VHV positions [22,23]. After acceptance, VHVs receive a brief training on primary health care, health promotion, disease prevention, and health education [21,23].

Thailand has over 1.1 million registered VHVs [24], the majority of whom are women (female-to-male ratio 4:1) aged 40–60 [25]. Each VHV is usually responsible for 7–15 households [25]. Their duties include informing, advising, and educating villagers on health issues and primary care, conducting routine screenings (e.g., malaria and blood sugar), collecting health data to inform national health programs, taking leading roles in community development and empowerment activities, and providing emotional and social support [21]. This multifaceted role positions VHVs as central actors in the healthcare system in Thai communities.

The effectiveness of community-based interventions relies heavily on individual behaviour, engagement, and adherence to preventive measures [26]. The Health Belief Model (HBM) provides a conceptual framework to investigate why an individual is motivated to take action to prevent or control health risks [27], and has been widely applied to studies such as adherence to COVID-19 precautionary measures in China [28], use of protective work equipment in Thailand [29], HIV prevention in Iran [30], and the zoonoses preventive practices by livestock farmers in Nepal [31].

Few studies, however, have integrated the HBM and One Health principles into community-based interventions. This integrated approach addresses both individual perceptions and behaviours and broader ecological and health factors, offering great potential to increase awareness and health education, ultimately reducing zoonotic pathogen spillover. Here, we describe a community-based One Health educational programme co-created with rural communities in Thailand, entitled Saan Suk (in Thai, “Weaving Health”), that addresses individual behaviour, health, and ecological drivers of zoonotic spillover risk and contributes to pandemic preparedness and prevention, and a protocol for a cluster randomised trial aiming to evaluate its effects. The programme was co-developed using a Human-Centred Design (HCD) approach [32], an iterative, participatory methodology that prioritises end-user needs, preferences, and contextual constraints, and is widely used in global health intervention development [33] and was piloted in the community. In this study, we aim to evaluate the effects of Saan Suk on targeted knowledge, behavioural, and attitudinal outcomes. This protocol describes the design and methods of a cluster-randomised controlled (cRCT) trial to assess these effects compared with current practice. If effective, the Saan Suk programme is intended to be suggested for integration into the existing national VHV training programme as part of routine training and community health promotion activities in Thailand.

## Materials and methods

### Aims, study design, and settings

We will implement the Saan Suk cRCT in rural villages of Chanthaburi province, eastern Thailand. We hypothesise that community members in villages allocated to the Saan Suk intervention will show better knowledge and understanding of zoonotic spillover, transmission pathways, risk factors, perceived susceptibility and severity, and preventive behaviours compared with community members in villages continuing the current practice. Therefore, the primary objective of the Saan Suk cRCT is to evaluate whether the Saan Suk educational programme (intervention) improves community members’ knowledge and understanding of zoonotic spillover, transmission pathways, risk factors, perceived susceptibility and severity, and preventive behaviours, as informed by the Health Belief Model, as well as socio-ecological drivers as informed by the One Health approach. The secondary objectives of the Saan Suk cRCT are to: 1) assess changes in attitudes, perceived susceptibility, and perceived severity of zoonotic disease risks, in line with the Health Belief Model; 2) assess whether the intervention changes self-reported preventive behaviours that reduce direct and indirect contact with wildlife, domestic animals, and potentially infectious animal tissues; and 3) evaluate whether hands-on training and skill-building delivered by VHVs enhances community members’ self-efficacy to translate knowledge into preventive practices.

The Saan Suk trial is a parallel-arm, cluster-randomised superiority trial evaluating the effectiveness of the Saan Suk intervention on the primary and secondary outcomes. Villages are the unit of randomisation and the Saan Suk intervention allocation. Villages will be allocated equally, i.e., using an 1:1 ratio, to the intervention or control arm using simple randomisation. The cluster design was selected to minimise intervention spillover between participants living in the same village and to reflect the planned mode of intervention delivery through village-level health structures.

The target population will be adult community members living in rural villages in Chanthaburi Province. Chanthaburi has approximately 536,000 inhabitants [34] spread across 10 administrative districts, with livelihoods primarily based on nature, and the local economy based on agriculture, fruit cultivation, and livestock raising. These social and ecological conditions make it a suitable setting for testing the effectiveness of the community-based One Health knowledge intervention aimed at preventing zoonotic diseases. The Saan Suk trial will be conducted in two districts of Chanthaburi: Pong Nam Ron District, including the sub-districts Thap Sai, Nong Takhong, Khlong Yai, and Thep Nimit, and Soi Dao District, including the sub-districts Thung Khanan, Saton, and Sai Khao. Both districts border Cambodia. Fig 1 presents the CONSORT flow diagram for the Saan Suk cRCT.

**Fig 1 pone.0354989.g001:**
[figure not shown]
Trial flow diagram showing village randomisation, household recruitment, intervention delivery, and outcome assessment in the Saan Suk cluster-randomised controlled trial.

### Sample size calculation

The sample size for the Saan Suk cRCT was calculated based on the primary outcome, i.e., the knowledge score, scaled to 0–100. Parameters were derived from a cross-sectional survey conducted in Chanthaburi in November 2024 (n = 687), with a resulting mean knowledge score of 57.35 and standard deviation (SD) of 15.23. An intracluster correlation coefficient (ICC) of 0.028 was obtained by fitting a random-intercept linear mixed-effects model with village as the clustering variable. Assuming a two-sided significance level of α = 0.05 and 90% power, the trial is powered to detect differences in mean knowledge scores between the intervention and control arms at the post-intervention assessment. We parameterised the expected effect using Cohen's *d* of 0.40 [35], corresponding to approximately six points on the 0–100 knowledge scale, based on the estimated SD from the cross-sectional survey. This effect size is considered a small-to-moderate improvement in educational intervention research, and it is viewed as a meaningful and achievable change in population knowledge over a short period.

Sample size adjustments accounted for clustering, a 15% allowance for both individual- and cluster-level attrition, and a 5% inflation to account for potential contamination. Based on these assumptions and operational feasibility, the final design includes 24 clusters (villages), with 12 clusters per arm, with an average cluster size of 42 participants (i.e., 6 VHVs per village, visiting 7 households each), resulting in a total sample size of 1008 individuals (504 per arm) (Fig 1).

### Participants

Villages (clusters) and VHVs delivering the intervention will be assessed for eligibility based on the following inclusion and exclusion criteria. Villages will be eligible if (1) they are classified as rural and located within the study area; (2) they have at least six active VHVs; (3) they are accessible by vehicle (a van); (4) they are located at least 2 km from other participating villages; (5) their Village Heads provide written informed consent; and (6) they are considered feasible for study implementation based on prior scoping visits and survey data. Villages will be excluded if they meet any of the following criteria: (1) located in urban areas or outside the study area; (2) not feasible for implementation due to security concerns (e.g., armed conflict, civil unrest) or lack of governmental approval; or (3) located less than 2 km from another participating village.

VHVs will deliver the Saan Suk educational programme to participating households in their assigned villages. VHVs will be eligible if they meet all of the following criteria: (1) are currently active in their role and regularly serving at least seven households; (2) have been living in the selected village for at least six months prior to enrollment and intending to remain for the duration of the trial; (3) are registered in the national VHV registry; (4) participate in routine VHV training at the local hospital; (5) are aged ≥18 years; (6) are able to provide informed consent; and (7) are willing to participate in a 2–3 days training programme. VHVs will be excluded if they meet any of the following criteria: (1) are unable to provide informed consent; or (2) decline or withdraw consent at any stage of the study.

Households are eligible if they are permanent households in a participating village, are assigned to a VHV included in the trial procedures, have at least one adult household member aged 18–80 years, and the Household Head provides informed consent for household participation. Households are not eligible if they are uninhabited or not permanently occupied, are assigned to a VHV not included in the trial procedures, have no household member aged 18–80 years, or the Household Head does not provide consent.

Adult household members are eligible if they are 18–80 years old, legally able and mentally competent to provide informed consent, have lived in the village for more than 6 months before enrollment, can participate in the educational intervention and outcome assessments, and provide written informed consent. Adult household members are not eligible if they are younger than 18 years or older than 80 years, have lived in the village for less than 6 months, are unable to provide informed consent or meaningfully participate, do not speak Thai, are physically unable to attend study activities, are under the influence of alcohol or drugs during study procedures, or decline or withdraw consent.

### Recruitment

Before cluster enrollment begins, the trial coordination team will select the required number of clusters from the list of villages in each district, along with their geolocations. Villages will be randomly chosen from the eligible sampling pool, with the additional requirement that participating villages must be at least 2 km apart to reduce the risk of intervention spillover between the trial arms. To account for potential refusals or withdrawals, two additional villages per district will be preselected as replacements. Further, we will select the VHV Head and randomly five VHVs for each village using the government VHV registry, following the eligibility criteria. The VHV Head in each village will ensure study implementation. In each village, we will further pre-select two replacements in case selected VHVs decline to participate.

Before cluster and participant enrollment, we will conduct a scoping and engagement visit to secure the necessary institutional and local permissions, ensure alignment with national and provincial priorities, and facilitate stakeholder collaboration. We will recruit villages for the Saan Suk cRCT through existing district-level administrative structures. We will send official invitation letters from Khon Kaen University to the Chief of District supporting the study implementation and to the Village Heads of the selected villages, presenting the study objectives, procedures, risks, and benefits, as well as the list of selected VHVs for participation.

Further, we will invite the Village Heads and VHV Heads of the selected villages to an in-person meeting at the two district offices. During these meetings, the trial research team will introduce the objectives and procedures of the Saan Suk trial. Village Heads and VHV Heads who agreed, on behalf of their villages, to participate will be invited to sign informed consent forms.

Following the village and VHV Head enrollment, we will return to the villages to explain the meeting outcomes and the study implementation to the randomly selected VHVs from the registry and obtain their agreement to participate in the study using informed consent procedures. Participating VHVs will provide information on the households they are usually responsible for, including the number of people in each household, the number of eligible adults, their ages, and names. This data will serve as a sampling frame for the random selection of seven households to participate in the trial procedures. The number of households that a VHVs regularly visits can range from 7 to 15. The data manager in the coordination site will receive a digitised list of household IDs, including the names and ages of the adults. The data manager will then randomly select seven households for participation using a pre-developed function in *R* software that facilitates random selection of the needed number from the provided sequence, i.e., 7 from n = 1–15. The data manager will provide an additional two households for replacement in case the selected household does not agree to participate. VHVs will inform them about the study and obtain verbal consent to participate in the trial.

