### Intervention and comparator

The Saan Suk is a community-based One Health educational programme designed to be delivered by trained VHVs during routine household visits in rural Thailand. It was co-developed with community stakeholders in rural Thailand, including Village Heads, VHVs, and community members, using the HCD approach [32]. Community input and feedback guided the development of the intervention materials, delivery format, culturally appropriate content, and field feasibility considerations during the design and pilot phases. The Saan Suk programme is multimodal and includes community engagement, educational videos, leaflets, calendars, and practical items, including soap, biodegradable gloves, wet tissues, and cutting boards, used as learning tools to be delivered by VHVs to introduce and reinforce key information and support preventive behavioural practices. Household members will receive intervention materials comprising nine illustrated leaflets and three animated videos covering One Health topics, such as zoonotic diseases and spillover, forest and wildlife protection, market safety, safe food preparation, and how to safely handle livestock, bats, and wildlife. These materials complement the explanations and discussions provided by the VHVs and can be revisited by household members after the visits (see examples of the pamphlets in S2 Fig). All materials are culturally adapted, use plain language, and depict familiar community settings and daily life situations encountered in rural Thailand.

Different modes of the Saan Suk programme serve distinct but complementary functions integrated into each visit: 1) videos and leaflets establish risk identification and knowledge of transmission mechanisms; 2) practical demonstrations and handouts of protective items build self-efficacy and behavioral skills by providing tangible, actionable strategies; 3) calendars and take-home artefacts (such as cutting boards reinforcing food separation practices) serve as environmental cues and reminders that extend learning beyond the visit, supporting habit formation and maintenance of safer behaviours; and collectively, 4) these materials articulate the benefits of protective actions through concrete, contextualised examples relevant to household and agricultural settings (Fig 2).

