Socio-demographic and experiential variables are collected to describe the study population and adjust for potential confounding. The questionnaire was reviewed by experts from Thailand and Europe and piloted with a small sample (n = 24) of the target population in November 2025, in Khon Kaen Province, Thailand, to assess its clarity and feasibility. Minor revisions were made before field implementation. The questionnaire was developed based on several key publications identified through a literature review, including PREDICT project questionnaires [36,37], WHO-UNICEF WASH household survey [38], and studies on health literacy among pet owners and livestock farmers, mosquito-borne diseases, wildlife trade, and bushmeat consumption in Africa [39] and Southeast Asia [40–43]. It is divided into five sections: (1) general information and participant ID generation; (2) knowledge, attitudes, self-efficacy, and behaviour related to zoonotic disease and spillover risk; (3) exposure to animal and environmental risks across different sites usually visit (home, temple, garbage dump, water body, agricultural field, and forest) and animal contacts reported; (4) socio-demographic and livelihood characteristics; and (5) contamination and process monitoring questions.

Primary and secondary outcomes will be assessed among recruited household members in both arms during the week following completion of intervention delivery. The Village Heads will invite participants to attend the assessment interview session in the community centre. The trained trial team will obtain informed consent when it has not been obtained previously. The interview will be conducted using a structured questionnaire and will last 45–60 minutes.

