### Statistical analyses

The statistical analysis will follow the intention-to-treat (ITT) principle. All eligible and consenting household members selected for outcome assessment will be analysed according to the randomised allocation of their village, regardless of intervention exposure, adherence, protocol deviations, or withdrawal from intervention activities. The village is the unit of randomisation, while outcomes are measured at the individual participant level. All analyses will therefore account for clustering at the village level. The allocation groups will remain masked to the statistician where feasible, until the primary analysis code and outputs are finalised. The primary comparison will be between villages allocated to the Saan Suk intervention and villages allocated to the current practice. All effect estimates will be presented with 95% confidence intervals. Statistical significance will be assessed using two-sided tests with an alpha level of 0.05.

A per-protocol analysis will be conducted as a sensitivity analysis. Here, we will include participants in intervention villages who received at least three or four planned visits, and participants in control villages with no documented exposure to Saan Suk-specific materials or training content.

Baseline characteristics will be summarised by cRCT arm to assess the comparability of the randomised groups and to describe the study population. Because randomisation is conducted at the village level, baseline balance will be assessed at both the cluster and individual levels. Cluster-level baseline characteristics include sub-district, distance to neighbouring study villages, number of registered VHVs, and relevant ecological characteristics, i.e., land use classes (e.g., vegetation, agricultural areas) and land-use interfaces where contact between people and wildlife may occur. Individual-level baseline characteristics will include age, sex, education, income, occupation category, household size, prior experience of zoonotic infectious diseases, and prior awareness of zoonotic diseases. The baseline assessment of the outcomes will not be conducted due to restricted operational feasibility. The background characteristics will be presented as means and standard deviations or medians and interquartile ranges for continuous variables, and as counts and percentages for categorical variables. Cluster size variation will be described and considered in sensitivity analyses.

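### The random draw stops at the household although one adult per household is scored, so the person tested can be settled after allocation and differently by arm

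*Protocol article*

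**What the plan says.** The Recruitment section describes a chain of selection: villages at random, the VHV Head plus five randomly chosen VHVs, then seven households per VHV with two reserves. Of the household information that VHVs supply, it says: "This data will serve as a sampling frame for the random selection of seven households to participate in the trial procedures". On the last step it says "The data manager will then randomly select seven households for participation using a pre-developed function in" R. The information needed to go one level lower is already collected: "The data manager in the coordination site will receive a digitised list of household IDs, including the names and ages of the adults". No use of that list to choose a person is stated.

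The Sample size calculation section gives an "average cluster size of 42 participants (i.e., 6 VHVs per village, visiting 7 households each"). Under Participants, a household qualifies with at least one adult aged 18–80, so it may hold several.

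The programme is addressed to the household: "Household members will receive intervention materials comprising nine illustrated leaflets and three animated videos". Under Informed consent, intervention-arm members consent before the programme starts, whereas control-arm individuals are asked at the outcome assessment. Under Primary and secondary outcomes, "The Village Heads will invite participants to attend the assessment interview session in the community centre". Table 1 does not mark Village Heads as blinded to the allocation. The Statistical analyses section sets the analysis population: "All eligible and consenting household members selected for outcome assessment will be analysed according to the randomised allocation of their village". The same section states that outcomes are not measured at baseline.

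**The concern.** Village randomisation protects the comparison only if the people scored in each village are chosen by a process that cannot depend on the arm. Here the last choice, which adult of the household is tested, has no stated rule, and the steps around it are open to knowledge of the allocation. In an intervention household, an obvious person to come forward is the adult who took part in the Saan Suk visits and has a reason to attend a test on their content. Control households have no Saan Suk visits, and the person tested there may first be identified when consent is sought at the interview.

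If that happened, the primary contrast would mix the programme effect with a difference in who was tested. The target of estimation would also move from adults of visited households towards adults who attended. With no baseline knowledge score, neither could be seen in the data. Adjustment for age group, sex, education and occupation would remove only the part that those variables carry, not interest or motivation.

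**Working it through.** **Step 1. Reproduce the plan's figure.** Inputs from the Sample size calculation section: 24 villages (12 per arm), 6 VHVs per village, 7 households per VHV.

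- Per village: 6 × 7 = 42.
- Per arm: 12 × 42 = 504.
- Total: 24 × 42 = 1,008.

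All three match the article. They close only with one scored person per household.

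**Step 2. Look for the rule that picks that person.**

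| Section | What it fixes | Does it choose the adult? |
|---|---|---|
| Recruitment | Random households; adults' names and ages are listed | No |
| Participants | Eligibility of adults, the same in both arms | No; several may qualify |
| Informed consent | Consent before the programme (intervention) or at assessment (control) | No; timing differs by arm |
| Primary and secondary outcomes | Recruited members are assessed; the Village Head invites | No |
| Statistical analyses | The analysis set is consenting members selected for assessment | Presupposes a selection, gives no method |
| Table 2 | Baseline variables of household members in week 3, after randomisation in week 1 | No |

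**Step 3. What an arm-dependent choice would do (illustration).** Inputs from the article: SD 15.23, ICC 0.028, 12 villages per arm, two-sided α 0.05. Assumptions made here: 42 respondents per village, or 36 after roughly 15% loss (42 × 0.85 = 35.7); a village-level t test with 24 − 2 = 22 degrees of freedom; and the size of the bias, for which the documents give no figure.

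Standard error of the arm difference: SE = SD × √(2 × [1 + (m − 1) × ICC] / (12 × m)).

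- m = 42: design effect 1 + 41 × 0.028 = 2.148; SE = 15.23 × √(2 × 2.148 / 504) = 1.41 points.
- m = 36: design effect 1 + 35 × 0.028 = 1.98; SE = 15.23 × √(2 × 1.98 / 432) = 1.46 points.

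Probability of a significant result with no true effect (noncentral t, noncentrality = bias / SE):

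| Assumed differential | Points | m = 36 | m = 42 |
|---|---|---|---|
| none | 0 | 5% | 5% |
| 0.1 SD | 1.52 | 17% | 18% |
| 0.2 SD | 3.05 | about 51% | 54% |

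A shift of 1.5 points is a quarter of the 6-point target (1.5 / 6 = 25%).

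**Step 4. Room for the fix.** With a true 6-point effect the same formula gives power of about 97.5% at m = 36 and 98% at m = 42, so some extra non-response is affordable.

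**The case against.** The case against has five parts.

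- **Condensation.** An article may leave the within-household rule to the full protocol, and the flow diagram is not shown. Both the consent and the analysis text speak of members selected for assessment, so some selection is presupposed. This stands in part: a rule may exist elsewhere. But the article is specific down to the R function for households, and the steps it does state around the gap differ by arm.
- **One adult per household is inferred.** True: it follows from the arithmetic, and 42 is called an average. It is nevertheless the only reading on which 1,008 closes.
- **Attenders against anyone available.** A reader might infer that the trial will compare programme attenders with unselected control adults. The documents do not support that. The analysis disregards exposure and adherence, and the missing-data plan compares people by number of visits received, so incompletely exposed respondents are expected. Intervention-arm members consent before the visits. Control VHVs also make household visits, control respondents must also come to the community centre, and Village Heads are said to invite participants, not to choose among a household's adults. This objection stands: the arm-dependent choice is possible, not planned.
- **Size.** The 0.1 and 0.2 SD differentials have no source in the documents and ignore covariate adjustment. One might also argue that a 6-point effect in attenders halves to 3 points in a randomly drawn adult. That needs two adults, one attending and nothing passed on, while leaflets and other materials stay in the home for later use. It is an extreme case and is not relied on here.
- **Sequencing.** Table 2 places randomisation in week 1 and household enrolment in weeks 2–3, so a draw strictly before allocation is known may need rescheduling. This stands and shapes the fix.

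**Conclusion.** The concern holds as a gap that should be closed before recruitment starts. The numbers imply one scored adult per household, the stated random selection ends one level above that, and the consent timing, the invitation route and the definition of the analysis set allow the respondent to be settled after allocation and differently by arm. The planned comparison of selection, consent and refusal rates between arms would describe such a difference but not prevent it.

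The false-positive rate of about 17–18% in place of 5% depends on an assumed 0.1 SD differential together with the article's SD, ICC and number of villages. It shows how little bias matters at an SE of 1.4–1.5 points and is not a forecast. The point is one to fix, short of a finding that the primary comparison is invalid as planned.

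**What to change.** - **Recruitment.** When the data manager draws the seven households and two reserves per VHV, the same R function also draws one named eligible adult in each, from the list already supplied. The rule is the same in both arms. The draw is done before any visit and, where the schedule allows, before the allocation is revealed. If the allocation is already known, a computer draw from the full list still keeps the choice out of local hands.
- **Primary and secondary outcomes.** Village Heads invite from this named list, with no substitution within the household once visits have begun.
- **Statistical analyses.** The intention-to-treat set is defined as these pre-drawn adults, whatever visits they attended. An absent adult counts as a missing outcome under the existing missing-data plan.

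If the full protocol already contains such a rule, stating it in the Recruitment section is enough.

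Cost: a small addition to the selection function and new wording in three sections. Drawing before the allocation is revealed would also mean collecting the household lists earlier than Table 2 implies. The sample size is unchanged at 24 × 6 × 7 × 1 = 1,008. Some named adults will be unavailable, so non-response will rise somewhat; the 15% attrition allowance and power of about 97.5% at 36 per village leave room. Non-response should be watched, because the article mentions agricultural work and seasonal mobility and lists more than 20–30% missing primary data as a possible ground for stopping the trial.
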